#### Safety assessment

To evaluate the safety of the intervention, the occurrences of serious adverse events and treatment-related adverse events associated with RAGT and CGT will be recorded. Serious adverse events will be monitored for five specific events based on the guidelines [32]. Upon confirmation of a serious adverse event, the principal investigator will promptly report it to the Institutional Review Board and the Ministry of Health, Labour and Welfare. Treatment-related adverse events will be documented for occurrences such as skin injuries and falls. In the event of an adverse event, the therapist responsible will prepare an adverse event report that will include the name of the adverse event, the date of incidence, a detailed description of the course of the adverse event, the treatment for the adverse event, and the outcome following treatment. A report will be generated for each serious adverse event or treatment-related adverse event and compiled upon participant discharge.

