### Blinding

Due to the differing treatment programs between the RAGT and CGT groups, it will be challenging to blind participants and therapists with respect to group assignment. Therefore, only the assessors will remain blinded. To quantify the effectiveness of blinding, we will ask the blinded assessors to identify each participant’s group assignment at the conclusion of all assessments.

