### Analytical methods

Feasibility results will be reported using descriptive statistics. Recruitment, enrollment, adherence, and retention rates will be computed with 95% confidence intervals. The adverse events and their frequencies will be recorded. Any exclusions or dropouts, along with their reasons and stages of occurrence, will also be recorded. The success of blinding will be detailed as a percentage of correct guesses.

The primary outcome measure will be the incidence of gait independence during the intervention period. The cumulative incidence of gait independence will be analyzed using the Kaplan–Meier method, and the log-rank test will evaluate the significance of differences in the Kaplan–Meier curves between groups. Cumulative incidence of gait independence events at the end of the intervention, along with the median duration from baseline to gait independence attainment, and the restricted mean survival time until the end of the intervention will be calculated. Additionally, to supplement the initial treatment effect analysis, differences will be evaluated using the generalized Wilcoxon test. Individuals who do not achieve gait independence during the intervention period will be censored. Secondary clinical outcomes will encompass gait performance measures, physical function, and activity outcomes at baseline, 4 weeks, 8 weeks, and discharge, alongside the intervention dose. Comparisons between the two groups will utilize the chi-square test for categorical variables and either Student’s *t-*test or Mann–Whitney *U* tests for continuous variables. To evaluate the potential effectiveness of the intervention and gather data useful for future trial design, we will estimate the effect size for the time elapsed from baseline to achieving gait independence, specifically estimating the hazard ratio as a relative measure of the likelihood of achieving gait independence over time.

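### Non-serious adverse events are recorded only if treatment-related, so the safety frequencies in the two arms can reflect differing attribution

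*Protocol article*

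**What the plan says.** The Abstract states that adverse events under both kinds of training are documented in order to evaluate the safety of both. The rule for doing so is in the Safety assessment section:

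- Scope of recording: "the occurrences of serious adverse events and treatment-related adverse events associated with RAGT and CGT will be recorded".
- Non-serious events: "Treatment-related adverse events will be documented for occurrences such as skin injuries and falls".
- Author of the report: "the therapist responsible will prepare an adverse event report that will include the name of the adverse event". The other listed contents are the date, the course, the treatment given and the outcome. Relatedness is not on the list.
- Which events lead to a report: "A report will be generated for each serious adverse event or treatment-related adverse event and compiled upon participant discharge".

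On masking, the Blinding section says that "it will be challenging to blind participants and therapists with respect to group assignment", and concludes: "Therefore, only the assessors will remain blinded". The Safety assessment section gives these assessors no part in adverse-event reporting.

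On analysis, the Analytical methods section says only: "The adverse events and their frequencies will be recorded".

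**The concern.** Relatedness is normally a property recorded about an event. Here, for non-serious events, it decides whether the event is recorded at all. A fall judged to have nothing to do with training does not enter the data, so nobody can later review that judgement or recount the events under a different rule.

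Equal attribution in the two arms cannot be assumed. RAGT participants wear a robotic leg, an obvious suspect for a skin injury that the CGT arm lacks. They also receive conventional gait training every day and 120 minutes of non-gait rehabilitation, so the source of many events will be uncertain. Staff who know the arm may resolve that uncertainty differently in the two groups.

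What is at stake is the safety description that this pilot passes on to a larger trial. A difference, or the lack of one, in falls and skin injuries could come from attribution and not from how often events happen. Unrecorded events cannot be recovered at analysis.

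**Working it through.** The documents give no adverse-event figure to reproduce, so the check is first a reading of the text and then an illustration.

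**Reading**

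1. The opening and closing sentences of the Safety assessment section name the same two classes: serious events and treatment-related events. Neither covers an event that is both non-serious and unrelated.
2. Falls and skin injuries are mentioned only as examples within the treatment-related class.
3. The listed report contents do not include relatedness, so on this text it is settled outside the report.
4. No one is named as judge of relatedness. The therapist who writes the report is unblinded. Anyone other than an outcome assessor is outside the only group stated to be blinded.
5. Serious events form a separate class with no clear relatedness condition, so the problem is confined to non-serious events.

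**Illustration**

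Inputs:

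- 32 participants (Sample size section), taken as 16 per arm. The allocation ratio is not stated, so equal arms are an assumption.
- The same true risk *p* of a non-serious fall or skin injury in both arms, with at most one event per participant (assumed).
- Probability *a* that an event is judged treatment-related, which may differ by arm (assumed).

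Expected recorded events in an arm = 16 × *p* × *a*. With equal *p*, the expected ratio, RAGT to CGT, is *a*(RAGT) / *a*(CGT). The true risk cancels.

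Take *p* = 4/16:

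- Attribution 90% in RAGT, 50% in CGT: 4 × 0.9 = 3.6 against 4 × 0.5 = 2.0. The ratio is 3.6/2.0 = 1.8 and the difference 1.6 events.
- Attribution reversed: 2.0 against 3.6, ratio 2.0/3.6 = 0.56.
- Equal attribution, or recording whatever the cause: ratio 1.00.

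Other assumed attribution pairs, with the spurious difference in recorded risk for true risks of 20% and 50%:

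| Attribution RAGT / CGT | Expected ratio | Difference at *p* = 20% | Difference at *p* = 50% |
|---|---|---|---|
| 90% / 70% | 1.29 | +4 points | +10 points |
| 90% / 50% | 1.80 | +8 points | +20 points |
| 90% / 30% | 3.00 | +12 points | +30 points |
| 50% / 90% | 0.56 | −8 points | −20 points |

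**Comparison with chance**

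In the 3.6 against 2.0 case the recorded risks are 0.225 and 0.125. The variance of the difference in counts is 16 × 0.225 × 0.775 + 16 × 0.125 × 0.875 = 2.79 + 1.75 = 4.54, a standard deviation of about 2.1 events. The spurious 1.6 events is smaller than that. Unlike chance variation, it would not average out with more participants recorded under the same rule.

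**The case against.** **The text may not impose a filter.** The sentence on skin injuries and falls can be read as listing the event types that make up the category. The sentence introducing the therapist's report and the one in Analytical methods carry no relatedness condition. This has some force: the wording is not uniform. But the section's last sentence restricts reports to serious or treatment-related events, which agrees with its first. If the authors intend every fall and skin injury to be reported, that sentence still needs correcting.

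**The therapist is not said to judge relatedness.** This is right. A reader might infer that the treating therapist decides which events count, but the documents assign that therapist the writing of the report and leave the judgement unassigned. The concern needs only that no blinded person is given the task.

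**The full protocol may settle it.** Who judges causality, by what criteria and on what form are details an article may leave out, and their absence is not the criticism. The criticism is of the recording scope that the article states.

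**Little depends on these counts.** This also stands. The Analytical methods section plans descriptive frequencies and no formal between-arm safety test. Safety is not among the four progression criteria, and the Discussion calls the clinical findings exploratory. Even so, the frequencies are the whole of the planned safety result.

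**The size is circular.** The 1.8 is the assumed 90% divided by the assumed 50%. It shows how the mechanism works, not how large the bias will be.

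**Conclusion.** The concern holds in limited form. As written, the rule makes relatedness a condition for recording non-serious events, and no blinded person is given a role in applying it. The resulting frequencies can therefore differ between arms when the true rates do not, or hide a real difference. The expected ratio under equal true rates is the ratio of attribution probabilities, 0.56 to 1.8 for the assumed 50%/90% and 90%/50%. The actual size and direction are unknown, because the documents give neither event rates nor attribution rates.

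Two stronger readings are not supported. A reader might infer that a planned safety comparison is invalidated, but no such test is planned and no progression decision uses these counts. A reader might also take the trial to be the first use of RAGT in acute stroke, with safety data that would carry special weight. The Discussion claims only, to the authors' knowledge, the first study of its effect on gait independence in that population.

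This is a worthwhile, inexpensive improvement to the safety data of an exploratory pilot, not a defect in its main results.

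**What to change.** Change the Safety assessment section in three ways:

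1. Record a pre-listed set of events, at least falls and skin injuries, in both arms over the same defined period (for example from randomisation to discharge), whatever the suspected cause. Take events outside therapy sessions from existing hospital records.
2. Make relatedness a field on the report and no longer a condition for having one.
3. State in Analytical methods that all-cause frequencies will be shown by arm, with treatment-related events as a subset.

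The cost is a few changed sentences, one extra field, a few more report forms and a check of existing records. No adjudicator is needed. The change does not remove detection and reporting by staff who know the arm, which the report of the trial should acknowledge. Recruitment is expected to run to March 31, 2026. For participants already enrolled, listed events not recorded at the time can be recovered only as far as hospital records allow.

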#### Clinical outcomes

The Standard Protocol Items: Recommendations for Interventional Trials (SPIRIT) diagram presented in Fig. 4 summarizes the data collection schedule. Furthermore, we have included the SPIRIT 2013 checklist as an additional file, comprising recommended items to address in a clinical trial protocol. Blinded assessors will perform assessments weekly after the baseline assessment until participants achieve an FAC score of ≥ 3. Continuous weekly assessments will be terminated once the participants achieve an FAC score of ≥ 3 or when they undergo the intervention for 8 weeks. However, assessments at 4 and 8 weeks and discharge will always be performed, regardless of whether an FAC score of ≥ 3 is achieved. The blinded assessments will be conducted by three physical therapists with > 10 years of experience. The assessors will confirm the assessment methods sufficiently prior to the commencement of the study.

**Fig. 4 Fig4:**
[figure not shown]
SPIRIT figure Note: * Items to be assessed if the Functional Ambulation Category score is ≥3. SIAS, Stroke impairment assessment set

The primary clinical outcome measures will include the number of days from the baseline assessment to the achievement of gait independence and the percentage of individuals achieving gait independence—operationally defined as an FAC score ≥ 3. In particular, this primary clinical outcome represents the most promising candidate for future clinical trial endpoints. Secondary clinical outcomes encompass gait parameters as assessed by velocity, stride length, and cadence in the 10-m walk test; 6-min walk distance; SIAS scores for lower limb motor and trunk function; total score on the Functional Independence Measure (FIM); and the number of steps taken during gait training during the intervention period. The FAC is a reliable and validated clinical measure of gait ability based on the amount of assistance needed [20, 21]. The 10-m walk test is a reliable and validated clinical measure of walking ability [33, 34], whereas the 6-min walk test is a reliable and validated clinical measure of motor endurance [35, 36]. The number of steps taken during gait training will be recorded manually by a therapist using a counting device. The SIAS serves as a reliable and validated index for assessing functional impairment in patients with stroke [17–19]. It accounts for motor function, tension, sensory function, range of motion, pain, trunk function, higher brain function, and muscle strength on the non-paralyzed side, with total scores ranging 0–72. The total score for SIAS motor items is calculated as the sum of the hip flexion, knee extension, and foot pat tests, with scores ranging 0–15 points. The FIM, which comprises 13 motor items and 5 cognitive items, is a proven reliable index for assessing independence in activities of daily living [37, 38]. Each item is rated on a scale of 1–7, with scores of 1–4 indicating the need for varying levels of physical assistance, a score of 5 indicating the need for supervision, a score of 6 indicating modified independence, and a score of 7 indicating complete independence. The FIM cognitive total is the sum of scores of the five cognitive items, ranging 5–35 points.

In addition, to understand participant characteristics, the following data will be collected at baseline: age; sex; height; weight; disease type; affected side; days post-stroke onset at admission, assessment, and discharge; National Institutes of Health Stroke Scale (NIHSS) score; GCS score; SIAS motor function scores for the lower extremities; trunk function; sensory function in the lower extremities; tone in the lower extremities; function in the lower extremities on the unaffected side; and visuospatial function. The NIHSS is a reliable and validated index for assessing stroke severity [39–41]; it evaluates consciousness, gaze, visual field, facial paralysis, paralysis of the extremities, ataxia, sensory disturbance, aphasia, dysarthria, elimination issues, and neglect, with scores ranging 0–42. A score of 0 is considered normal, while 42 indicates the most severe condition. The GCS consists of three items, namely eye opening, verbal response, and motor response. Eye opening is scored from 1 to 4, verbal response from 1 to 5, and motor response from 1 to 6. The total GCS score is defined as the sum of the scores of these three items, ranging 3–15, with 3 indicating severe impairment and 15 indicating normal responsiveness.

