### Participants

The inclusion criteria are as follows: (i) individuals aged 16–90 years, (ii) those with hemiplegia due to a first-ever supratentorial cerebral infarction or hemorrhage, (iii) those starting intervention within 7 days of stroke onset, (iv) those with severe lower extremity hemiparesis at the preintervention assessment (total score of ≤ 6 on the Stroke Impairment Assessment Set [SIAS] [17–19] motor items for lower extremities), (v) those with severe gait disorder at the preintervention assessment (score of ≤ 1 on the Functional Ambulation Categories [FAC] [20, 21]), (vi) those with sustained awareness at the preintervention assessment (eye opening score of 4 and motor response score of 6 on the Glasgow Coma Scale [GCS] [22, 23]), (vii) those with body weight of 35–100 kg, and (viii) those with height of 140–190 cm.

The exclusion criteria are as follows: (i) individuals with a history of stroke (except for individuals with no symptoms despite imaging findings indicating a history of stroke); (ii) those with pre-existing gait disorders due to neuromuscular or musculoskeletal diseases; (iii) those that participated in other interventional studies related to lower limb/trunk motor function and gait; (iv) those with a history of epileptic seizures within the past 2 years (including seizures caused by the current stroke); (v) those with cardiovascular or respiratory diseases that impede exercise therapy; (vi) those with uncontrolled hypertension; (vii) those with osteoporosis of the lower limbs or spine; (viii) those with heterotopic ossification in the lower extremities leading to limited range of joint motion; (ix) pregnant women or those with possibility of pregnancy; (x) those with infectious diseases requiring isolation; (xi) those with urinary or fecal incontinence that may compromise the robotic device through contamination; (xii) those unable to wear the robotic leg due to overweight, deformities in lower limbs, or pressure ulcers; and (xiii) individuals deemed unsuitable by the attending physician, principal investigator, or research assistants.

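### Walking-test outcomes appear to be measured only at FAC 3 or above, so a between-arm comparison among those measured would be selected by the primary event

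*Protocol article*

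**What the plan says.** Four statements in the protocol article bear on this.

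- **Measurement condition.** The note to Fig. 4 describes starred items as "Items to be assessed if the Functional Ambulation Category score is ≥3". The figure itself is not available, so the starred items cannot be read off.
- **Primary event.** The outcome text under Fig. 4 counts "the percentage of individuals achieving gait independence—operationally defined as an FAC score ≥ 3". The threshold is the same.
- **Secondary outcomes and their comparison.** The same text states: "Secondary clinical outcomes encompass gait parameters as assessed by velocity, stride length, and cadence in the 10-m walk test; 6-min walk distance"; SIAS, FIM and step counts follow. Analytical methods schedules "gait performance measures, physical function, and activity outcomes at baseline, 4 weeks, 8 weeks, and discharge" and compares arms using "either Student’s *t-*test or Mann–Whitney *U* tests for continuous variables".
- **Entry condition.** The Participants section requires a "score of ≤ 1 on the Functional Ambulation Categories" at the preintervention assessment.

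The Clinical outcomes section adds that the 4-week, 8-week and discharge assessments take place whether or not FAC 3 has been reached. For the primary analysis, Analytical methods says what happens to non-achievers: they are censored. For the secondary comparisons it says nothing about them.

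**The concern.** A walking test that is done only once FAC reaches 3 yields data only in participants who have had the primary event. That event occurs after randomisation, and the trial's hypothesis is that the robotic arm reaches it sooner. A two-group test on the measured participants then sets one selected subset against a differently selected one. If the robotic arm brings marginal patients over the threshold, those slower walkers enter its mean, while their counterparts in the conventional arm go unmeasured.

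Two things are at stake. The walking-speed and distance results could understate a real benefit, or point the wrong way, in just the situation where the intervention works on the primary outcome. The Discussion also intends to carry estimates of variability into the design of a later trial, and a walkers-only variance describes a selected group.

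A lesser point is that the collective schedule for secondary outcomes includes baseline. Everyone enters at FAC 1 or below, so an item conditional on FAC 3 can have no baseline value.

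**Working it through.** **Which items are starred.** Among the listed secondary outcomes, SIAS, FIM and the therapist's step count can be recorded in anyone. Only the 10-m and 6-min walks require the participant to perform a walking test. That the asterisk marks these two is an inference, though a strong one.

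**Inputs.** The plan states no effect size, SD or attainment rate for these outcomes, so there is no figure of its own to reproduce. From the documents: 32 participants (Sample size), taken as 16 per arm on the assumption of equal allocation, and a general gait-recovery range of 41–85% (Background), used only as a range for attainment. Assumed: shifts of 0.5 and 0.8 SD, normal latent recovery, and walking speed fully tied to recovery.

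**Numbers measured.** 16 × 0.41 = 6.6 and 16 × 0.85 = 13.6, so about 7 to 14 per arm would have walking data.

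**Attenuation.** Let recovery be N(0, 1) in the conventional arm and N(d, 1) in the robotic arm, with testing only above a cut-off c set by control attainment. Write λ(a) = φ(a) / [1 − Φ(a)]. The mean among those tested is λ(c) in the conventional arm and d + λ(c − d) in the robotic arm. For d = 0.5:

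| Control attainment | c | Robotic-arm attainment | Mean, conventional | Mean, robotic | Difference | Loss relative to 0.5 |
|---|---|---|---|---|---|---|
| 41% | 0.228 | 61% | 0.948 | 1.133 | 0.185 | 63% |
| 50% | 0 | 69% | 0.798 | 1.009 | 0.211 | 58% |
| 60% | −0.253 | 77% | 0.644 | 0.888 | 0.244 | 51% |
| 85% | −1.036 | 94% | 0.274 | 0.631 | 0.356 | 29% |

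A simulation of the same model gave 0.187 at 41% and 0.245 at 60%, hence about 0.19 to 0.25 SD. For d = 0.8 it gave 0.32 and 0.43 SD.

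**Looser tie between speed and recovery.** With correlation 0.7, the true speed difference for d = 0.5 is 0.349 SD. Among those tested it is 0.130 at 41% attainment and 0.171 at 60%. The proportional losses, 1 − 0.130/0.349 = 63% and 1 − 0.171/0.349 = 51%, are unchanged.

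**More walkers, same speed.** Suppose the intervention only lowers the recovery needed to reach FAC 3 and changes nobody's speed. The difference is then λ at the robotic arm's cut-off minus λ at the conventional arm's:

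- 41% v 60%: 0.644 − 0.948 = −0.30 SD
- 60% v 85%: 0.274 − 0.644 = −0.37 SD
- 41% v 85%: 0.274 − 0.948 = −0.67 SD

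**No effect at all.** With d = 0 at 41% attainment the simulated difference among those tested is 0.00. Under this model the distortion arises only when the intervention changes attainment.

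**Effect on the test.** With 16 per arm, d = 0.8 and speed fully tied to recovery, simulated Mann–Whitney power was:

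| Control attainment | All randomised, worst rank below FAC 3 | Only those at FAC 3 or above | Mean number tested, robotic v conventional |
|---|---|---|---|
| 41% | about 50% | about 13% | 11 v 7 |
| 60% | about 54% | about 23% | 14 v 10 |

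**The case against.** The strongest reply is that the article does not say in terms what is alleged. The figure is missing, so no text names the starred items. Analytical methods names the tests but does not confine them to walkers, and Mann–Whitney is compatible with worst-rank scoring. A condensed article may leave that rule to an analysis plan. The Clinical outcomes section also says the 4-week, 8-week and discharge assessments are always done, and these are the post-baseline time points analysed.

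Much of this stands. A reader might infer that the protocol states that the walking tests are confined to FAC 3 and that only walkers are analysed; neither is written down. It does not dispose of the point. The article itself gives the measurement condition, the time points and the tests, and together these lead most naturally to a comparison among those measured. The sentence on fixed assessments concerns visits, while the note concerns items. If the sponsor intends every item at those visits, the note needs correcting.

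The size is also open to challenge. Attainment of 41–85% comes from a general stroke figure, and at 85% the loss falls to 29%. Dividing by the SD among those tested, not the full-population SD, gives 0.32 SD at 50% attainment (1 − 0.32/0.5 = 36% loss) and a 16% loss at 85%. A reader might infer from the attenuation figures that a benefit would be reversed. They do not show that: every difference in that model is positive, and a deficit arises only under the separate assumption of more walkers with unchanged speed.

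On baseline, the schedule is one collective list for several kinds of measure. It does not specify a baseline test of walking speed, so only a clarification is needed.

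**Conclusion.** The point holds, conditional on the walking tests being the starred items. Read together, the Fig. 4 note and Analytical methods lead to a comparison of subsets selected by the event the intervention is meant to change. In the illustration a 0.5 SD benefit shows as about 0.19 to 0.25 SD at 41% to 60% control attainment, with less loss at higher attainment. A spurious deficit of 0.30 to 0.67 SD arises if only attainment changes. These figures rest on assumed effect sizes, a latent-normal model and equal allocation; they are not predictions for this trial.

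A reader might infer that the trial's main conclusions are compromised. The documents do not support that. These are secondary outcomes in a 32-person pilot whose clinical findings are declared exploratory and whose effect sizes will not be used directly to size the next trial. The time-to-FAC 3 analysis, SIAS and FIM are unaffected. Severity is moderate to minor, and confidence is moderate because the figure is missing.

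**What to change.** 1. State which items carry the asterisk, and reconcile the Fig. 4 note with the statement that the 4-week, 8-week and discharge assessments are always performed.
2. For velocity and 6-min distance at each fixed time point, compare all randomised participants by Mann–Whitney. Give those not tested because FAC is below 3 the tied worst rank. This is a score and not a literal 0 m/s, since FAC grades assistance and a value below 3 does not mean unable to walk. Report a win probability with a 95% confidence interval. Keep values missing for other reasons separate from this rule.
3. Report walkers-only velocity and distance, and stride length and cadence, descriptively, with the number measured per arm and no between-arm test. Label any variance taken forward as a walkers-only variance.
4. Clarify that the walking tests have no baseline value, because entry requires FAC 1 or below.

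This changes wording only and adds no assessments. The price is many ties, an estimate on the rank scale instead of in m/s or metres, and a comparison that partly repeats the primary outcome because it separates those above FAC 3 from those below. If the sponsor prefers not to accept that, item 3 applied to all walking-test measures is a sufficient minimum.

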We defined the “acute” phase as the period occurring within 7 days of stroke onset [14] and have planned a study to clarify the efficacy of RAGT initiated during this timeframe. We hypothesize that the initiation of RAGT in the acute phase would enable individuals to achieve gait independence more rapidly than with CGT. Early RAGT promotes motor learning and mitigates disuse by delivering high-intensity, task-oriented gait training from an early stage [9, 15]. To test this hypothesis, we aim to examine the following: (i) the feasibility of conducting a randomized controlled trial on RAGT for improving gait after acute stroke and (ii) obtaining preliminary estimates of the potential efficacy of RAGT for achieving gait independence during the acute phase.

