### Interventions

The study schedule is illustrated in Fig. 2. Participants will undergo the intervention during their hospitalization at Fujita Health University Hospital. The intervention will continue until participants achieve an FAC score of ≥ 3 or for up to 8 weeks from the start of training. Participants in both the RAGT and CGT groups will receive rehabilitation for 180 min per day, 7 days per week. Both groups will undergo gait training for 60 min per day [30] and non-gait training for 120 min per day. The RAGT group will undergo RAGT for 40 min per day and CGT for 20 min per day, for 6 days a week, with an additional 60 min of CGT once per week. The CGT group will undergo CGT for 60 min, 7 days per week (Fig. 2).

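### The step-count dose outcome runs over a period that ends at the primary event, so comparing it between arms mixes steps per day with time to success

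*Protocol article*

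**What the plan says.** All places are in the Methods of the protocol article.

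- **Clinical outcomes** lists as a secondary outcome "the number of steps taken during gait training during the intervention period". Therapists record the steps by hand with a counting device. No unit per day, per session or per fixed window is attached.
- **Interventions** fixes the length of that period: "The intervention will continue until participants achieve an FAC score of ≥ 3 or for up to 8 weeks from the start of training".
- **Clinical outcomes** uses the same threshold for the primary outcome: "the percentage of individuals achieving gait independence—operationally defined as an FAC score ≥ 3".
- **Analytical methods** places the secondary outcomes "alongside the intervention dose" and assigns Student's t-test or the Mann–Whitney U test to continuous variables. It mentions no adjustment for time on treatment.
- **Interventions** matches the daily time: "Both groups will undergo gait training for 60 min per day".

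The **Background** gives the expected direction, "We hypothesize that the initiation of RAGT in the acute phase would enable individuals to achieve gait independence more rapidly than with CGT", and the proposed mechanism, "delivering high-intensity, task-oriented gait training from an early stage".

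**The concern.** The event that ends the counting is the primary event. A participant who succeeds early stops accumulating steps early, so the length of the counting window is in effect the primary outcome.

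The hypothesis then pulls the count in two directions. If RAGT gives more intensive practice, its steps per day go up. If RAGT also works faster, its days of counting go down. A cumulative count multiplies the two, and a simple two-group test cannot separate them.

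Minutes of gait training are equal by design, so the step count is the one listed outcome in which a difference in practice intensity could show. Two misreadings are possible: that RAGT gave no more practice when it gave more each day, or that the arms differed in dose when only their time to success differed. The Discussion says the findings may lead to changes in the intervention parameters, so the step data could be used in that way.

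**Working it through.** **The plan's own figures.** The article gives no expected step count, no event-time assumption and no hazard ratio, so there is no dose figure to reproduce. Everything below is conditional on stated assumptions.

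**Model.** Total steps = steps per day × days on intervention. Assume that daily steps are constant within a participant and unrelated to time to success, that time T to FAC 3 or more is exponential with median m days, that FAC is read weekly, and that training is capped at 56 days (8 weeks). Then

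mean days = 7 × (1 + q + … + q^7) = 7 × (1 − q^8)/(1 − q), with q = 2^(−7/m).

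| Median m | q | q^8 | Mean days |
|---|---|---|---|
| 21 | 0.7937 | 0.1575 | 7 × 0.8425/0.2063 = 28.6 |
| 28 | 0.8409 | 0.2500 | 7 × 0.7500/0.1591 = 33.0 |
| 42 | 0.8909 | 0.3969 | 7 × 0.6031/0.1091 = 38.7 |

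Daily step ratio that RAGT needs merely to equal the CGT total:

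- 28 v 42 days: 38.7/33.0 = 1.17, or 17% more
- 21 v 42 days: 38.7/28.6 = 1.35, or 35% more

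**Wider range.** The Background cites recovery of gait in 41–85% of people after stroke. Using 41%, 60% and 85% as the CGT success rate at 8 weeks is an assumption. With weekly reading, hazard ratio 2 for success and a true daily ratio of 1.3:

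| CGT success at 8 weeks | Mean days, CGT v RAGT | Ratio of days | Ratio of total steps (× 1.3) |
|---|---|---|---|
| 41% | 45.0 v 36.9 | 0.82 | 1.07 |
| 60% | 38.8 v 28.7 | 0.74 | 0.96 |
| 85% | 28.2 v 18.1 | 0.64 | 0.84 |

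A real 30% daily advantage is largely hidden in the first row and reversed in the other two. Stopping in continuous time instead of weekly gives 1.03, 0.91 and 0.75.

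**Simulation.** Assumptions: 16 per arm, weekly reading, between-participant coefficient of variation of daily steps 30%, Mann–Whitney at two-sided 0.05, 1,500 runs per scenario.

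- CGT success 60%, hazard ratio 2, true daily ratio 1.3: the mean total is lower under RAGT in about 57% of trials. The test on totals rejects in about 6%, the test on steps per day in about 66%.
- Equal daily rates, hazard ratio 2: the test on totals rejects in about 17%, 25% and 32% of trials for CGT success of 41%, 60% and 85%. The test on steps per day stays near 5%.
- Hazard ratio 1, true daily ratio 1.3: the median ratio of totals is about 1.30, so there is no systematic bias. There is only lost power: about 27%, 19% and 14% for totals against 64%, 66% and 68% for steps per day.

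**Does a daily rate remove the dependence?** Only if daily steps do not change with recovery. Suppose they double linearly over 56 days, identically in both arms. The average over a stay of D days is 1 + D/112. For mean stays of 33.0 and 38.7 days this gives 1.29 and 1.35, a ratio of about 0.96 although the arms do not differ. The distortion is much smaller than in the total but not zero. A window common to both arms avoids it.

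**The case against.** - **The article never says that steps are summed.** The phrase about the intervention period could simply say when therapists count, and the unit could be set in the full protocol. This stands in part. A reader might take a total as a stated fact; it is an inference from a count over a period with no denominator. It is still the plainest reading, and it is combined with a stated two-group comparison.
- **Cumulative steps are a legitimate measure of dose received.** This stands. The article calls the quantity dose, not intensity, and plans no test of mechanism. A reader might infer that totals are invalid or that the trial will conclude that RAGT gave no more practice; the documents support neither. What fails is reading a difference in totals as a difference in training intensity.
- **The exposure difference will be visible.** Analytical methods commits to median time to independence and restricted mean survival time to the end of the intervention, which approximates mean days on treatment apart from dropout, missed sessions and any gap between baseline and first training. This partly stands. It lets a careful reader see unequal exposure but does not adjust the dose comparison.
- **The sizes come from assumptions.** This stands. A constant hazard from the first day is doubtful in people who enter with FAC 1 or less and severe paresis.
- **The stakes are low.** This stands. It is one secondary outcome in a pilot whose Discussion calls the clinical findings exploratory and does not intend to use effect sizes directly to size the next trial.

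**Conclusion.** The point holds in a limited form. As worded, the dose outcome is most naturally a cumulative count over a window that closes at the primary event. If the arms differ in time to FAC 3 or more, as hypothesised, an unadjusted comparison of that count mixes steps per day with time to success and can hide or reverse a true difference in intensity. If times to success are equal, nothing is systematically biased.

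The 17% and 35% figures show what plausible differences in event time could do; they are not estimates for this trial. It would go too far to infer that a daily advantage of that size will be erased, because the article gives neither event times nor step rates.

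The matter is a cheap improvement to an exploratory secondary outcome. The primary analysis, the feasibility criteria and the target of 32 participants are unaffected.

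**What to change.** 1. Define the between-group dose comparison as steps per gait-training day over a common early window, for example the first training week. The first scheduled weekly assessment comes only after that week, so nearly all participants should still be training.
2. Report steps per training day over the whole period as support, noting that it can still drift with length of stay if daily steps rise with recovery.
3. Report total steps descriptively in each arm, beside days on intervention, without reading the difference as one of intensity.

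**Cost.** One definition changes and no new assessment is needed. Counts must be stored by day or session; the article says only that they are recorded manually, so this should be confirmed while recruitment is open. Treatment and its stopping rule stay as they are.
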